### Objectives and trial design {7} {8}

The Optimizing Primary Care Tools for Incontinence MAnagement (OPTIMA) project is a cluster randomized trial of a four-pronged practice-based incontinence intervention conducted across four health systems in Southern California (Fig. 1). It was created in response to the Agency for Healthcare Research and Quality (AHRQ) initiative: Improving Nonsurgical Treatment of Urinary Incontinence among Women in Primary Care (RFA-HS-21-001). The overall goals of the project are to improve primary care management of incontinence, reduce unnecessary referrals to specialists, and improve patient-centered outcomes. Herein, we describe the detailed methods of this clinical trial, which is reported in accordance with the SPIRIT 2013 (Standard Protocol Items: Recommendation for International Trials) guidelines [10].

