#### APP co-management

Intervention PCPs also have the option to refer study patients to an Advanced Practice Provider (APP) co-manager with expertise in UI. If referred, the patient is scheduled for a visit (telemedicine or in-person) with the APP, who provides follow-up teaching and non-surgical management according to standard clinical practice. APPs can also refer participating patients to a urology/urogynecology specialist as clinically indicated.

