#### Secondary provider outcomes

Data on referral rates are also collected at the 6-month chart abstraction to assess overall specialty referral rates and the presence of an appropriate delay of referrals, in which referrals are placed only after first-line treatment is initiated.

At baseline, providers complete a demographic questionnaire and a modified version of the Pelvic Floor Awareness and Knowledge Survey (Fig. 3). The PFAKS is a 31-item validated questionnaire assessing knowledge of three pelvic floor disorders: pelvic organ prolapse (11 items), stress urinary incontinence (SUI) (10 items), and overactive bladder (OAB) (10 items) with questions on condition pathophysiology, management, and quality of life for these conditions [17]. The modified PFAKS excludes the 11 pelvic organ prolapse items.

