### Sample size {14}

All power estimates were performed assuming mixed-model regression modeling to account for the nested study design (patients within providers within offices) using PASS 2020 software [27]. As randomization will occur at the office level, power was computed assuming an average of 3 providers per office with an intra-cluster correlation of 0.04 (consistent with previous reports for process-of-care outcomes [28]) and a correlation of 0.16 across patients within each provider. Preliminary data found the average baseline quality of care to be 40% with a standard deviation of 20% [8, 18]. Therefore, to detect a change of 6% in total scores at an alpha level of 0.05 with 80% power, the study will require at least 720 patients from 48 offices (360 patients from 24 offices per study arm; see Fig. 1).

We conservatively estimate this sample size can detect a minimum odds ratio of 0.52, which is equivalent to a decrease in referral rates from 60 to 44% between the two treatment arms of the study, with 80% power at the 0.05 significance level. For patient-reported outcomes, our preliminary data had an average score of (± SD) of 35 (± 20) for the UDI-6 and 18 (± 20) for the IIQ-7. The study is powered to identify a difference of 6 points or greater in each of the two measures between study arms.

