## Statistical methods

### Statistical methods for primary and secondary outcomes {20a} {20b}

The primary outcome of quality of care will be measured by constructing aggregate QI scores ranging from 0 to 100%, as described by McGlynn et al. [30]. 5% of all records will be re-abstracted to evaluate inter-rater reliability using Gwet’s AC1 correlation [31, 32]. Given the potential differences in patient and provider demographics between the private, public-private, and public county health systems, factors such as patient race/ethnicity, provider sex, and provider specialty will be assessed via a simplified mixed model regression, incorporating random effects to account for clustering. Analysis will be conducted using SAS with significance set at *p* = 0.05.

A chi-square test will be used to compare patient enrollment between health systems to evaluate the potential impact and efficacy of phone vs. email screening as a recruitment tool. Patient referral rate to specialty care in both intervention and routine care arms will be assessed using cluster logistic regression. Appropriate delay of referral is measured as a dichotomous outcome (timely vs. premature referral) with proportion between groups analyzed via a chi-squared test.

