### Methods in analysis to handle protocol non-adherence and any statistical methods to handle missing data {20c}

PCPs are given a 6-month window for each patient participant to address their UI. If no UI-related discussion or treatment occurs within this timeframe, the patient’s UI is considered an “unaddressed case.” This can be factored into PCP’s aggregate score by adding to the total number of visits with the patient to the denominator for their proportion of encounters where QI met vs. encounters eligible for QI. Unaddressed cases are also recorded for potential inclusion as secondary outcomes or in subgroup analyses, depending on trial outcomes.

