## Trial status

Patient recruitment is currently underway, and outcomes data collection for both patients and PCPs is estimated to be complete by the end of 2025.

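### Appropriate delay of referral is, on its plain reading, compared among referred women only, so the tested share need not track premature referrals per enrolled woman

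*Protocol article*

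**What the plan says.** Under Secondary provider outcomes, the 6-month chart abstraction is to capture overall referral rates and also "appropriate delay of referrals, in which referrals are placed only after first-line treatment is initiated". The statistical methods section ({20a} {20b}) then fixes the scale and the test: "Appropriate delay of referral is measured as a dichotomous outcome (timely vs. premature referral) with proportion between groups analyzed via a chi-squared test". The sentence just before it treats the other referral outcome differently: "Patient referral rate to specialty care in both intervention and routine care arms will be assessed using cluster logistic regression".

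Referral is itself a target of the trial. The objectives are to "improve primary care management of incontinence, reduce unnecessary referrals to specialists, and improve patient-centered outcomes". Under eConsult referrals, a specialist screens intervention-arm referrals and, where basic first-line care is missing, sends recommendations to consider before referring. Intervention PCPs may also send patients to an advanced practice provider (APP), "who provides follow-up teaching and non-surgical management according to standard clinical practice". The Sample size section gives a minimum detectable odds ratio of 0.52, "equivalent to a decrease in referral rates from 60 to 44% between the two treatment arms of the study".

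**The concern.** The outcome has two values, timely referral and premature referral, and no section assigns a woman who is never referred to either. Taken as written, the proportion is computed among women who were referred. That group forms after randomization, and the intervention acts on who enters it. Randomization therefore does not protect the comparison.

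The stated goal of treating first so that fewer women need a specialist also works against the measure. Suppose an intervention-arm woman would have been referred after first-line care, but first-line care or APP co-management succeeds and she needs no referral. She leaves both the timely count and the denominator, and her good result lowers the timely share.

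At stake is whether a named secondary outcome answers the question that the trial poses about referrals. The overall referral rate is analysed separately, but it does not distinguish premature from timely referrals. No planned test addresses premature referral per enrolled woman.

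**Working it through.** **Inputs from the Sample size section.** 360 women per arm; referral 60% against 44%, which is a detectable difference and not a forecast; odds ratio 0.52; a 6-point difference in quality score with SD 20; correlations of 0.04 (office) and 0.16 (provider); 3 providers per office. The Abstract's 15 patients per office gives 5 per provider.

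**Assumption.** The premature share of referrals is not in the article. I take 50% and vary it.

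**Reproducing the plan's figures.**
- Odds ratio: (0.44/0.56) / (0.60/0.40) = 0.786/1.5 = 0.524, against 0.52 stated.
- Sample size: 175 per arm without clustering. Design effect 1 + (5 − 1) × 0.16 + 5 × (3 − 1) × 0.04 = 2.04. Then 175 × 2.04 = 357 per arm, 714 in total, against 720 stated.

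The planning numbers hold. The issue is the denominator of this one outcome.

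**Who is in the comparison at these rates.** Referred: 360 × 0.60 = 216 and 360 × 0.44 = 158.4. Without a value: 144 and 201.6.

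**General relation.** Let R be the referral rate and f the premature share among referred women. The planned test compares f between arms (the timely share is 1 − f). Premature referrals per enrolled woman are R × f. These fall whenever f(intervention)/f(routine) is below R(routine)/R(intervention) = 0.60/0.44 = 1.36. So the premature share can stay level, or rise by a factor of up to 1.36, while fewer women are referred prematurely.

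**Equal shares.** With f = 0.50 in both arms, the timely share is 50% against 50% and chi-square is 0. Premature referrals per woman go from 0.60 × 0.50 = 30% to 0.44 × 0.50 = 22%, or 108 to 79 women. For other equal shares the planned contrast is still zero and the fall per woman is 16 × f points: 4, 8 and 12 points for f = 0.25, 0.50 and 0.75.

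**Other ways the fall could be split, starting from f = 0.50 (30% premature and 30% timely per enrolled woman).**

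| Intervention arm, per enrolled woman | Timely share, routine to intervention | Premature referrals per woman |
|---|---|---|
| Premature 24%, timely 20% | 50% to 0.20/0.44 = 45.5% | 30% to 24% |
| Premature 14%, timely 30% (only premature removed) | 50% to 0.30/0.44 = 68.2% | 30% to 14% |
| Premature 30%, timely 14% (only timely removed) | 50% to 0.14/0.44 = 31.8% | 30% to 30% |

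In the first row the share points the wrong way, but weakly: 108/216 against 72/158.4 gives chi-square 0.76, p about 0.38. In the second row the share moves in the right direction. In the third row chi-square is 12.4 (p = 0.0004), with 108 premature referrals in each arm. None of these p-values allows for clustering.

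**The case against.** Several points on the other side have weight.

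- **The denominator is inferred.** The article never says that only referred women count, and a condensed article may leave such a rule to the analysis plan. That stands as a limit on certainty. But the article does fix a two-valued outcome in which both values are referrals. If all enrolled women were meant, the definition has no place for those never referred and needs correcting anyway.
- **The conditional share is a legitimate process measure.** Whether first-line treatment had started when a referral was placed is a sensible question, and it resembles the eligible-case scoring of the quality indicators. With the overall referral rate beside it, a reader can work back to premature referrals per woman. This supports keeping the share as a description. It does not make a comparison of two differently selected groups an estimate of the intervention's effect.
- **The mechanism favours the intervention.** Academic detailing and eConsult triage aim mainly at referrals made without first-line care. If they remove mostly those, the share improves.
- **The inputs are illustrative.** The 60% and 44% are detectable rates, and the premature share is assumed.

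A reader might infer that the planned test is likely to show harm, pointing to the p = 0.0004 case. The documents do not support that. The case needs the whole fall to come from timely referrals, has no fewer premature referrals at the assumed 50% share, and ignores clustering. The example with a worse share and clearly fewer premature referrals gives only p about 0.38.

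**Conclusion.** The point holds in this form: on the plain reading, the test is made within a group defined after randomization that the intervention is meant to shrink, so its result need not agree with the effect on premature referral per enrolled woman. The firmest consequence is a missed effect. With equal premature shares the test is null at any share above zero, while premature referrals per woman fall in proportion to referrals overall: 30% to 22% at an assumed 50% share, and by 4 to 12 points for shares of 25% to 75%, all at the detectable rates of 60% and 44%. A reversed sign is possible but not certain, and an improved share is equally possible. The conclusion rests on the inferred denominator and on the intervention changing the referral rate; if that rate does not change, the two measures agree in direction. One secondary outcome is affected. The primary quality-indicator score is not.

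**What to change.** Define the tested outcome for every enrolled woman as referred before first-line treatment was initiated, yes or no. Analyse it with the cluster logistic regression already named for the referral rate, in place of a chi-squared test that ignores office clustering. Report by arm, per enrolled woman: not referred; referred after first-line treatment; referred before it. Keep the timely share among referred women as a descriptive figure.

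No new abstraction is needed, because referral and its order relative to first-line treatment are already required for the planned outcome. Trial status says that "outcomes data collection for both patients and PCPs is estimated to be complete by the end of 2025", so the change belongs in the analysis plan before the data are analysed.

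There are two costs. First, a woman who is neither treated nor referred counts as not prematurely referred. Section {20c} already records such unaddressed cases ("If no UI-related discussion or treatment occurs within this timeframe"); show them separately within the not-referred group, and read the result beside that count and the overall referral rate. Second, the change corrects what is measured but does not guarantee a significant result: 30% against 22% with 360 women per arm has about 69% power before any allowance for clustering, and less after it.

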### Interim analyses {21b}

Not applicable.

### Methods for additional analyses (e.g., subgroup analyses) {20b}

Between-group differences across sites will be assessed for primary and secondary outcomes via subgroup analyses. All analyses will be conducted using SAS, with statistical significance set at *p* = 0.05. Adjustments for multiple comparisons will be applied where necessary.

### Methods in analysis to handle protocol non-adherence and any statistical methods to handle missing data {20c}

PCPs are given a 6-month window for each patient participant to address their UI. If no UI-related discussion or treatment occurs within this timeframe, the patient’s UI is considered an “unaddressed case.” This can be factored into PCP’s aggregate score by adding to the total number of visits with the patient to the denominator for their proportion of encounters where QI met vs. encounters eligible for QI. Unaddressed cases are also recorded for potential inclusion as secondary outcomes or in subgroup analyses, depending on trial outcomes.

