Electronic alerts for providers vary by site and include either an interruptive alert or a non-interruptive alert (banner). Electronic alerts are timed to fire within the EHR system during the PCP’s visit with patient participants, alerting the PCP to the patient’s positive screen for bothersome UI. Electronic alerts are the only aspect of the CDS toolset provided to both arms of the study. Since the primary outcome of interest is the quality of UI care provided (and not whether or not a UI-related conversation occurs in the first place), electronic alerts are implemented since embarrassment may contribute to patients’ reluctance to initiate UI conversations.

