### Outcomes {12}

#### Primary outcome: quality-of-care measures

The primary outcome of this trial is provider quality of care. Provider quality of care in both arms is measured via retrospective chart abstraction at baseline and again for each respective patient participant. Care provided over a 6-month timeframe is evaluated for adherence with 13 primary care UI QIs we previously developed, to allow adequate time to comply with the QIs [8] (Table 1). For each chart abstraction, a given eligible indicator is scored as a dichotomous measure (met vs. not met). Aggregate scores are measured as proportions: encounters where patients receive the recommended care vs. total encounters where patients are eligible for specific QIs. The results will be reported as percentages ranging from 0 to 100%.

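### Whether and in what unit unaddressed cases enter the primary QI score is left open, and their secondary or subgroup use is made to depend on trial outcomes

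*Protocol article*

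**What the plan says.** The primary outcome is an aggregate QI score from 0 to 100%, taken from 6-month chart review. Under Primary outcome in Outcomes {12}, the scoring is first per chart and per indicator: "For each chart abstraction, a given eligible indicator is scored as a dichotomous measure (met vs. not met". The aggregate is then described in encounters: "encounters where patients receive the recommended care vs. total encounters where patients are eligible for specific QIs". That section does not mention patients whose incontinence was never taken up.

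They appear only in section {20c}: "If no UI-related discussion or treatment occurs within this timeframe, the patient’s UI is considered an “unaddressed case". For the primary score the text is permissive: "This can be factored into PCP’s aggregate score by adding to the total number of visits with the patient to the denominator". For other uses it says: "Unaddressed cases are also recorded for potential inclusion as secondary outcomes or in subgroup analyses, depending on trial outcomes".

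The section on clinical decision support tools explains why the alert goes to both arms. The primary outcome is the quality of care given, "and not whether or not a UI-related conversation occurs in the first place".

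Sample size {14} gives the scale: "Preliminary data found the average baseline quality of care to be 40% with a standard deviation of 20", and the design is meant "to detect a change of 6% in total scores at an alpha level of 0.05 with 80% power".

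**The concern.** Three things are fixed badly in the text itself.

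1. **Inclusion is optional.** A reader cannot tell whether an unaddressed patient counts in the primary score. Under Recruitment {15}, every enrolled woman has said that she has new or worsening bothersome incontinence and wants to raise it with her provider, so she belongs to the trial population. Whether it is then addressed is a post-randomisation event. Coaching, note templates and order sets exist only in the intervention arm. They could change both whether the topic is taken up and whether it is charted. Excluding unaddressed patients then compares groups selected after randomisation.

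2. **The unit is inconsistent.** An addressed patient brings her eligible indicators to the denominator. An unaddressed patient brings her visits. Depending on how visits are added, she may count for a small fraction of an addressed patient or for several times as much.

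3. **Other uses depend on results.** Whether unaddressed cases become a secondary outcome or a subgroup factor is tied to how the trial turns out. The Discussion says that providers, patients, study staff and chart abstractors are not blinded, which makes a rule fixed in advance more important.

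**Working it through.** **The plan's own figure.** Inputs from Sample size {14} and the Abstract: difference 6, SD 20, alpha 0.05 (taken as two-sided), power 80%, 3 providers per office, 15 patients per office (so 5 per provider), office correlation 0.04, within-provider correlation 0.16.

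- Unclustered: 2 × 20² × (1.96 + 0.84)² / 6² gives 175 per arm.
- Design effect: 1 + (5 − 1) × 0.16 + (3 − 1) × 5 × 0.04 = 2.04.
- 175 × 2.04 = 357 per arm, 714 in total, against the stated 720. Power at 360 per arm is 80.5%.

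The stated size reproduces, so 6 points is a fair yardstick.

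**One provider.** Assume 4 addressed patients with 10 eligible QIs each, half met, and 1 unaddressed patient with 2 visits. The score is 20/40 = 50.0% if she is excluded, 20/42 = 47.6% if her visits are added once, and 20/50 = 40.0% if her 10 QIs count as not met.

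**Across arms.** Let s be the score in addressed patients, u the unaddressed share, and w the denominator weight of an unaddressed patient relative to an addressed one. She adds nothing to the numerator, so

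score = s(1 − u) / [(1 − u) + u·w].

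Take s = 40 in both arms (the baseline figure in {14}). The article gives no unaddressed rate, so assume 30% in routine care and 15% in intervention.

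| Rule | w | Routine care | Intervention | Difference |
|---|---|---|---|---|
| Excluded | 0 | 40.0 | 40.0 | 0 |
| Two visits added once, 10 eligible QIs | 0.2 | 40 × 0.70/0.76 = 36.8 | 40 × 0.85/0.88 = 38.6 | 1.8 |
| All eligible QIs not met, counted once | 1 | 28.0 | 34.0 | 6.0 |
| Two visits added to every QI denominator | 2 | 40 × 0.70/1.30 = 21.5 | 40 × 0.85/1.15 = 29.6 | 8.0 |

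The second row depends on the assumed 10 eligible QIs. With 8 it is 38.3 − 36.1 = 2.2, and with all 13 it is 38.9 − 37.5 = 1.4.

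**Range over the assumed rates, full counting (w = 1).**

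- Equal care at 40%: the difference is 40 × (gap in unaddressed rates). A 10-point gap gives 4.0 and a 15-point gap gives 6.0.
- True scores 46 versus 40, equal rates: 6 × (1 − u) gives 5.4, 5.1 and 4.8 at 10%, 15% and 20%.
- True scores 46 versus 40, with 20% unaddressed in routine care and 10% in intervention: 41.4 − 32.0 = 9.4. With those rates reversed: 36.8 − 36.0 = 0.8.

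**Power if unaddressed patients score zero.** With 20% unaddressed, SD = √[0.8 × (20² + 40²) − 32²] = √576 = 24. The effective size is 360/2.04 = 176 per arm and the standard error is 24 × √(2/176) = 2.56. Power is about 65% for a 6-point difference and about 47% if the difference dilutes to 4.8.

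**The case against.** A reader might infer more than the text supports, in four ways.

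- **That the primary scoring rule will be picked after results are seen.** The outcome-dependent clause governs only secondary and subgroup use. For the primary score the fault is the permissive verb. The Discussion mentions detailed scoring rubrics, and these or an analysis plan not shown may settle the rule. That does not cure what the article states.
- **That the article's own options differ by 6 points.** They do not on the simplest reading. Leaving patients out and adding two visits once differ by about 1.8 points under the assumed 30% versus 15%. The 6.0 needs a zero-scoring rule that the article does not propose.
- **That visits are simply the wrong unit.** Outcomes {12} also speaks of encounters, so visits are not foreign to it. The fair description is that the unit is inconsistent, and that its readings can under-weight or over-weight an unaddressed patient.
- **That the trial is underpowered at 65%.** That figure is a cost of scoring unaddressed patients as zero, not an error in the sample size, which reproduces.

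Two design points also count against a large effect. The alert reaches both arms, and enrolled women already want to discuss their symptoms. Both should narrow any gap in unaddressed rates, but neither guarantees equality when templates, coaching and order sets are given to one arm only. Finally, the article says that its interest is not in whether a conversation occurs. Scoring unaddressed patients as zero in the primary analysis sits uneasily with that and would need justification.

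**Conclusion.** The point holds in this form. Inclusion of unaddressed cases in the primary score is optional, the unit is inconsistent with the scoring definition, and their secondary or subgroup use is openly tied to results. These are statements in the article, not details left to an analysis plan.

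The size is conditional on rates that the article does not give. Under 30% versus 15% unaddressed and equal care of 40%, the choice of rule moves the arm difference from 0 to about 1.8 points on the simplest reading of the visit rule. It moves it to 6.0 under full counting, and further if visits enter every indicator's denominator. With equal rates of 10–20%, full counting costs a 6-point effect only 0.6 to 1.2 points. Six points is therefore an illustration and not a bound. Because the trial is unblinded and the target is itself 6 points, the rule should be settled before outcomes are seen by arm.

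**What to change.** Before any outcome is summarised by arm:

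1. Commit to one mandatory rule for the primary score, in the per-patient eligible-QI unit. One example is to score every enrolled patient over the 6-month window. If she is unaddressed, the QIs that apply to any woman with bothersome incontinence count as not met, and the indicator satisfied by not offering a drug gets no default credit.
2. Justify the chosen rule against the stated focus on quality of care rather than on whether a conversation took place. If the addressed-only score is preferred as primary, state the selection risk.
3. Name the other score as a sensitivity analysis.
4. Make the percentage unaddressed, by arm, a fixed secondary outcome.
5. Delete the visit-count rule and the clause that ties secondary or subgroup use to trial outcomes.
6. If unaddressed patients are scored as not met, restate the power with an SD and a difference that include them.

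The cost is wording and a change to the scoring program, with no new data. The restated power may be clearly lower: at an assumed 20% unaddressed it is about 65% for 6 points, or about 47% for 4.8.
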